#### Data collection and data sources

Table 1 and Table 2 describes the patient-level and clinician-level factors that we hypothesise may be associated with inappropriate imaging.

**Table 1 Tab1:** Patient-level factors being measured that may be associated with inappropriate imaging

Factor	Questionnaire items	Timing				
		*First visit*	*Follow up visits*	*3-month Q*	*6-month Q*	*12-month Q*
Age	Single questionnaire item	X				
Sex	Single questionnaire item	X				
Education level	Single questionnaire item	X				
Socio-economic status	Two questionnaire items: Postal code and education level	X				
Race/ethnicity	Single questionnaire item	X				
Living arrangement	Single questionnaire item	X				
Insurance status	Single questionnaire item	X				
Compensation status (workplace injury or motor vehicle)	Single questionnaire item	X				
Patient expectations of imaging	Single questionnaire item	X	X			
Patient beliefs about imaging	Two questionnaire items [43]	X				
Duration of low back pain	Single questionnaire item	X				
Previous history of low back pain	Single questionnaire item	X				
Low back pain intensity	Single questionnaire item (pain right now)	X	X	X	X	X
Leg pain intensity	Single questionnaire item (pain right now)	X	X	X	X	X
Recovery expectations	Single questionnaire item	X	X			
Previous back surgery	Single questionnaire item	X				
Previous medication and non-medication treatment	Single questionnaire items	X				
Previous imaging	Single questionnaire item	X				
General Health	Single questionnaire item	X	X			
Physical activity level	Single questionnaire item	X				
Overweight or obesity	Two questionnaire items: Self-reported height and weight	X				
Possible pathological cause of back pain (fracture, infection, cancer, cauda equina syndrome)	Questionnaire items about: Trauma; History of cancer; Unexplained weight loss; IV drug user; Long term use of oral steroids	X	X	X	X	X
Anxiety	Two questionnaire items [73]	X	X			
Depression	Two questionnaire items [73]	X	X			
Confidence in ability to work and to live a normal lifestyle	Two questionnaire items	X	X			
Disability	Questionnaire items: Roland Morris Q [74]	X		X	X	X
STarT Back risk category	Questionnaire items: STarT Back questionnaire [75, 76]	X		X	X	X
Fear avoidance	Single questionnaire item 14 from the Tampa Scale for Kinesiophobia (TSK) [77]^a^	X	X			
Pain Catastrophizing	Single questionnaire item 3 from Pain Catastrophizing Scale (PCS) [78]^a^	X	X			
Patient satisfaction	Single questionnaire item of global perceived effect		X			
Adverse events	Single questionnaire item [79]		X			

^a^Asked as part of STarT Back questionnaire at first visit

**Table 2 Tab2:** Clinician-level factors predictive of inappropriate imaging being investigated, all measured via baseline clinician questionnaire

Factor	Questionnaire items
Age	Single questionnaire item
Sex	Single questionnaire item
Years in practice	Single questionnaire item
Clinician type (family doctor, chiropractor, physiotherapist)	Single questionnaire item
School of entry-to-practice training (for everyone); program of family medicine training (for family doctors only)	Single questionnaire item
Access to imaging (onsite or offsite)	Single questionnaire item asked as part of a list of items about onsite services
Ownership of imaging facilities	Single questionnaire item
Self-identification as having a speciality in back pain	Single questionnaire item [80]
Clinician fear avoidance beliefs	Single questionnaire item: 14 from the Tampa Scale for Kinesiophobia (TSK), modified for clinician [81]
Average time spent with patient	Single questionnaire item
Type of manual technique modalities practiced (for chiropractors)	Single questionnaire item
Beliefs on usefulness of imaging	Single item on questionnaire
Knowledge of imaging guidelines	Single item on questionnaire

### Encounter data

After each patient consultation during the data collection period, participating clinicians will complete a handwritten 1-page encounter form (see Additional file 1: Appendix 3) for each of 25 consecutive consenting eligible patients with low back pain. There is one type of form for the initial encounter, and another, briefer form, for any follow-up consultations for the same low back pain episode. The encounter form is a modified form previously used in a chiropractic setting to systematically collect clinical data [51]; chiropractors reported that completing the form took 2–3 min per patient. The encounter forms for this project were piloted by two chiropractors, three physiotherapists and two family practitioners, who each recruited between two to five patients with low back pain over a six week period. Only minor changes were made to the form after the pilot study.

At the time of the patient’s initial consultation clinicians will record: key history and clinical findings; working diagnosis; diagnostic imaging ordered/taken; interventions provided or recommended; who is paying for the consultation; and, OHIP number for linkage purposes. Follow up encounter forms will be completed for each visit for up to 6 weeks to determine if any clinical indications for imaging arise. Six weeks was chosen because this is the time when people with low back pain are likely to be recovered, if pain is persisting they have progressed to the sub-acute stage, or if they have a pathological cause this is likely to be definitively diagnosed [57].

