### Inappropriate imaging

The encounter, questionnaire and administrative data will be used to determine if any imaging ordered is inappropriate. We will apply a modified version of the American College of Radiology imaging appropriateness criteria for low back pain [59]. If any of the following situations occur, including signs or symptoms indicating suspicion of “red flag” conditions [60], imaging will be considered appropriate: infection, tumour, fracture, or cauda equina syndrome (Table 3). If the clinical, questionnaire and administrative data are not suggestive of any of these conditions, any lumbar imaging ordered will be deemed inappropriate.

**Table 3 Tab3:** Diagnostic imaging will be deemed inappropriate in the absence of these conditions that indicate a specific cause of low back pain [59]

Condition	Sign or symptom
Cancer	History of cancer; unexplained weight loss
Infection	Immunosuppression; intravenous drug use
Fracture	Prolonged use of corticosteroids; history of significant trauma; minor fall or heavy lift in a potentially osteoporotic or elderly individual
Cauda equina syndrome	Acute onset of urinary retention or overflow incontinence; faecal incontinence; saddle anaesthesia

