### Quantitative data analyses

Characteristics of clinicians, patients and encounters will be summarised using descriptive statistics. We will calculate imaging rates per 100 low back pain patients with 95% confidence intervals and we will determine imaging rates for each primary care profession. We will undertake multilevel logistic regression analysis to determine the effects of clinician- and patient-level factors on inappropriate imaging. Clinician-level factors assessed will include age, sex, profession type, location of clinician training, clinician years in practice, ownership of imaging facilities, knowledge of imaging guidelines, and time spent with patient. Patient-level factors measured at baseline will include age, sex, race/ethnicity, insurance status, living in a metropolitan area, beliefs about usefulness of imaging, education level, duration/severity of low back pain, and three month measurement of satisfaction with treatment and adverse events. Patients consulting each clinician will form a cluster and will be considered as the second level in the multilevel logistic regression. We will also conduct a marginal logistic regression analysis to investigate the effects of clinician- and patient-level factors on inappropriate imaging and estimate the association between inappropriate imaging and explanatory factors in the marginal model using Generalised Estimating Equations. The analysis will allow examination of differences in results from the two models and determine whether the conclusions depend unduly on the model assumptions.

### Methods for study 2

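### A red flag noted only on the treating clinician's form is enough to class an image as appropriate, so unequal recording could bias the clinician-level associations

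*Protocol article*

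**What the plan says.** Three sources classify an image: "The encounter, questionnaire and administrative data will be used to determine if any imaging ordered is inappropriate" (Inappropriate imaging). They combine so that all must be negative for an image to count against the clinician: "If the clinical, questionnaire and administrative data are not suggestive of any of these conditions, any lumbar imaging ordered will be deemed inappropriate".

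The clinical source is the encounter form, completed by the treating clinician after the consultation. At the first visit "clinicians will record: key history and clinical findings; working diagnosis; diagnostic imaging ordered/taken" (Encounter data). Later visits have a shorter form with a time limit: "Follow up encounter forms will be completed for each visit for up to 6 weeks to determine if any clinical indications for imaging arise".

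The patient source is given in Table 1, in the row on possible pathological causes: "Questionnaire items about: Trauma; History of cancer; Unexplained weight loss; IV drug user; Long term use of oral steroids". These items are asked at the first visit, at follow-up visits and at 3, 6 and 12 months. Table 3 also accepts signs that this row does not list. For infection it gives "Immunosuppression; intravenous drug use", of which only the second has a listed patient item. For cauda equina syndrome it gives "Acute onset of urinary retention or overflow incontinence; faecal incontinence; saddle anaesthesia", none of which has one.

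The administrative source (Administrative data) adds pathology that develops, defined by diagnoses at more than two visits.

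The multilevel model relates inappropriate imaging to clinician factors that include profession and "ownership of imaging facilities, knowledge of imaging guidelines, and time spent with patient" (Quantitative data analyses).

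**The concern.** The person whose traits are being studied supplies part of the information that decides the outcome. Suppose two groups of clinicians image the same kinds of patients equally often, but one group writes down more of the flags that are present. More of that group's images are then classed as appropriate, and its inappropriate rate is lower although its imaging is the same. With imaging and true flags held equal, the error has one direction: fuller recording can only lower the rate. A larger sample does not remove it.

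The project's goal is to inform knowledge translation strategies. An association of guideline knowledge, consultation time or profession with less inappropriate imaging would be read as a difference in ordering. If part of it came from how fully flags are recorded, the study would credit those traits with more than they do.

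**Working it through.** The protocol gives no figure for how often flags are present or recorded, so there is none to reproduce on this point. Two inputs come from Sample size justification: base imaging rates of 10 to 45%, and the 6-point difference between professions, used here only as a yardstick. The power claimed for that difference plays no part.

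**1. Which signs have a second source.** Table 3 set against the items listed in Table 1:

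| Condition | Signs in Table 3 | With a listed patient item | Without |
|---|---|---|---|
| Cancer | 2 | 2 | 0 |
| Infection | 2 | 1 | 1 (immunosuppression) |
| Fracture | 3 | 2 | 1 (minor fall or heavy lift, older or osteoporotic patient) |
| Cauda equina syndrome | 3 | 0 | 3 |
| Total | 10 | 5 | 5 |

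**2. Size, counting only flags that the clinician's form alone can supply.** Let p be the imaging rate and f the share of imaged patients with such a flag (assumed 10-30%). One group records 60% of these flags and the other 90% (assumed). Imaging and true flags are the same in both groups.

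False difference = p × f × (0.90 − 0.60)

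| p | f = 10% | f = 30% |
|---|---|---|
| 10% | 0.10 × 0.10 × 0.3 = 0.3 points | 0.10 × 0.30 × 0.3 = 0.9 points |
| 30% | 0.30 × 0.10 × 0.3 = 0.9 points | 0.30 × 0.30 × 0.3 = 2.7 points |
| 45% | 0.45 × 0.10 × 0.3 = 1.35 points | 0.45 × 0.30 × 0.3 = 4.05 points |

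**3. Size, with the patient items modelled explicitly.** Let r be the share of imaged patients with any true flag, s the clinician's recording rate, c the share of flags covered by patient items, and q the chance that a patient reports a covered flag. Then

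P(inappropriate) = p × [(1 − r) + r × (1 − s) × (1 − c × q)]

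and the gap between two groups is p × r × (difference in s) × (1 − c × q). Here s is 0.9 v 0.5, a wider contrast than in step 2. All of r, s, c and q are assumptions.

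| p, r | No patient items | c = 0.6, q = 0.8 (factor 0.52) | c = 0.8, q = 0.9 (factor 0.28) |
|---|---|---|---|
| 25%, 20% | 2.0 points (OR 0.89) | 1.0 point (OR 0.94) | 0.6 points (OR 0.97) |
| 25%, 40% | 4.0 points (OR 0.76) | 2.1 points (OR 0.86) | 1.1 points (OR 0.92) |
| 45%, 40% | 7.2 points (OR 0.72) | 3.7 points (OR 0.84) | 2.0 points (OR 0.91) |

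The patient items therefore remove about half of the gap or more. The first column does not describe this study and is shown only for contrast.

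The two calculations connect through f = r × (1 − c × q). With the factor 0.52, f = 30% needs r = 0.30 / 0.52 = 58% of imaged patients with a true flag, so the top of the range in step 2 is demanding. The bottom needs 0.10 / 0.52 = 19%. ICES diagnoses are left out of both formulas and would shrink the gap further.

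**4. What the sensitivity outcomes do.** If flags come only from patients and ICES, s drops out of the formula and the gap between the two groups is 0. If the outcome is any imaging, it equals p in both groups and the gap is again 0.

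**The case against.** The other side has several good points.

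- **Three sources.** A reader might infer that the classification rests on the ordering clinician's word. It does not. Patients report half of the Table 3 signs at every time point, and ICES adds diagnoses. This stands, and step 3 shows how much it matters.
- **Timing.** Imaging is followed for 12 months, but encounter forms stop at 6 weeks. Later images, and images ordered by other providers, do not rest on the orderer's own sheet in the same way. This stands and confines the concern mainly to the first 6 weeks.
- **Forms not shown.** The encounter form and patient questionnaires are in appendices that are not at hand. If the encounter form prompts for each flag, recording differences shrink. The Table 1 row names cauda equina syndrome in its label, so its item list may be condensed. The trauma item may also pick up some minor falls. It cannot be concluded that patients are never asked about the unlisted signs.
- **Recording or eliciting.** A clinician who never asks about flags and images anyway has imaged without a known indication, which the study wants to count. Part of the difference could therefore be real behaviour.
- **No evidence of unequal recording.** The protocol shows none by knowledge, time or profession, and clinicians are not told that imaging is the focus, which makes defensive recording less likely. Concealment does not equalise thoroughness, however.
- **Existing safeguards.** Imaging rates by profession are planned, and a secondary objective compares recommending of imaging by profession. These do not reach knowledge or time. The generalised estimating equations comparison tests model assumptions on the same outcome, so it cannot detect misclassification.
- **Scope.** Sensitivity analyses often sit in a statistical analysis plan, and their absence from an article is no fault. The point concerns the outcome rule and predictors that the article itself fixes. If an unseen plan already holds these checks, nothing more is needed.

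**Conclusion.** The concern holds in limited form. A flag on the clinician's form alone can reclassify an image, half of the Table 3 signs have no listed patient item, and the recorder's own traits are the predictors. Any difference in recording would push those associations towards looking protective.

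Under the stated assumptions the false difference is 0.3-0.9 points at 10% imaging and 1.4-4.1 points at 45%. Against the 6-point yardstick that runs from 0.3 / 6 = 5% to 4.05 / 6 = about two thirds. The upper figure needs high imaging, a large share of clinician-only flags and a 30-point recording gap, all together.

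A reader might go further and infer that an association with guideline knowledge would be an artefact. The documents do not support that: the bias is possible and its direction known, but neither its presence nor its size is shown. Nor do they show that guideline knowledge will dominate the resulting strategy, which is to draw on both the quantitative and the qualitative results. This is a cheap improvement to the analysis, not a defect that undermines the study.

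**What to change.** Add two sensitivity models and report them beside the main one, with the same predictors and clustering:

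- (a) any lumbar imaging as outcome, adjusted for the patient-reported red-flag items;
- (b) inappropriate imaging with red flags taken only from the patient questionnaire and ICES.

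Also tabulate clinician-recorded flag rates by profession and by guideline knowledge. These rates vary with case mix too, so they are context and not a test.

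If the estimates for knowledge, time or profession differ materially between models, state that the association may partly reflect how flags are elicited or recorded. Do not require an association to hold in both models. Model (a) counts appropriate imaging, so a clinician who images more flagged and fewer unflagged patients could show no effect there. Model (b) misses flags that only a clinician elicits. Both are checks and not replacements for the main model.

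The cost is two model runs and one table on data already collected.

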### Patient questionnaires

Patients will complete questionnaires at each visit for up to six weeks (Table 1 provides domains covered, and the Additional File (Appendices 4 and 5) includes the questionnaires). Patients will also complete online questionnaires at 3 months, 6 months and 12 months post-index visit (see Additional file 1: Appendix 6). Figure 1 documents the patient data collection time points throughout the study.

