### Administrative data

Participating patients will be followed for 12 months using Ontario health administrative data held by the Ontario Institute for Clinical Evaluative Sciences (ICES) to determine if any imaging was undertaken (plain x-ray, CT scan, MRI, fluoroscopy, positron emission tomography (PET) scan, ultrasound). Although plain x-ray, CT scan and/or MRI are most likely to be ordered for patients with low back pain, we will capture all related imaging to be comprehensive in the assessment of inappropriate imaging. ICES data will also capture whether a pathological condition develops (defined with diagnoses at more than two healthcare visits), and surgery and emergency visits related to such a condition.

Some imaging may not be captured by the administrative data. Approximately 12% of chiropractors take their own plain x-rays and this information will not be captured in ICES data [58]; completed encounter forms by these chiropractors will indicate whether they took lumbar x-rays, and this information will also be collected via the patient-completed questionnaires. Also, some patients in Ontario elect to go to a private facility outside Ontario and individually pay for imaging. This information will be captured via the patient-completed questionnaires.

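### Lumbar imaging is counted for 12 months, but clinician-recorded indications stop at six weeks, so some justified later imaging will be labelled inappropriate

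*Protocol article*

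**What the plan says.** **Imaging window.** Protocol article, Administrative data: "Participating patients will be followed for 12 months using Ontario health administrative data". The purpose is to find any imaging undertaken. No shorter window is given for the inappropriate-imaging rate.

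**Clinician-recorded indications.** Encounter data: "Follow up encounter forms will be completed for each visit for up to 6 weeks to determine if any clinical indications for imaging arise". The follow-up form covers consultations for the same episode. The section gives a reason for six weeks: by then a patient is likely to have recovered or become sub-acute, or, in its words, "if they have a pathological cause this is likely to be definitively diagnosed".

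**Patient-reported indications.** Table 1 marks possible pathological cause at the first visit, at follow-up visits and at 3, 6 and 12 months. It describes the content as "Questionnaire items about: Trauma; History of cancer; Unexplained weight loss; IV drug user; Long term use of oral steroids". Patient questionnaires confirms the late schedule: "Patients will also complete online questionnaires at 3 months, 6 months and 12 months post-index visit".

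**Administrative indications.** Administrative data says that the linked records will show whether a pathological condition develops, defined by diagnoses at more than two visits, with related surgery and emergency visits. Data access plan adds the cancer registry, claims and hospital data.

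**Classification rule.** Inappropriate imaging combines the three sources. Signs or symptoms that raise suspicion of a Table 3 condition make imaging appropriate. If none of the sources is suggestive, "any lumbar imaging ordered will be deemed inappropriate".

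**The concern.** The numerator of the first primary objective is lumbar imaging without an indication. Imaging is captured mostly through linked records for the whole year. The evidence that would justify an image weakens after week 6, because the clinician's findings are no longer collected.

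The rule treats the absence of suggestive data as the absence of an indication, whether the patient had no red flag or nobody recorded one. It also does not separate the index episode from a new one, so an image for a fresh episode at month 9 is judged on the same footing.

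At stake are the primary rate and the secondary comparison among professions. The error depends on who is imaged late and who answers the late questionnaires, and neither need be equal across professions.

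**Working it through.** The plan states no figure on this point, so there is nothing to reproduce. The check compares time windows, then item coverage, then gives an illustrative size.

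**1. Time windows**

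| Source | Index to 6 weeks | 6 weeks to 12 months |
|---|---|---|
| Clinician encounter forms | each visit | none |
| Patient red-flag items | each visit | 3, 6 and 12 months only |
| Administrative diagnoses | yes | yes |
| Imaging counted | yes | yes |

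Encounter forms are absent for 52 − 6 = 46 weeks, and 46/52 = 88% of the window. Two of the three sources continue, so this is the share without clinician findings, not the share without any indication data.

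**2. Item coverage after week 6**

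Split at its semicolons, Table 3 has 2 cancer + 2 infection + 3 fracture + 3 cauda equina = 10 entries. The items listed in Table 1 match 5: cancer history, weight loss, intravenous drug use, steroids and trauma. The other five are:

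- immunosuppression;
- minor fall or heavy lift in an elderly or osteoporotic person, which the trauma item may cover in part;
- urinary retention or overflow incontinence;
- faecal incontinence;
- saddle anaesthesia.

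**3. What the rule does with a late image**

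Take an image ordered in month 5 for suspected cauda equina syndrome that proves negative. No encounter form exists, and none of the listed questionnaire items asks about the symptoms. No diagnosis will then recur at more than two visits. Under Table 3 the image was appropriate; under the rule as written it is counted as inappropriate. A missing late questionnaire has the same effect on an indication that the listed items would have caught.

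**4. Illustrative size**

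Overcount per 100 patients = 100 × imaging rate × share of imaging after week 6 × share of that imaging with a true indication missed by all sources.

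- Imaging rate: 10 to 45% (Sample size justification), taken here as a 12-month rate, which the protocol does not state.
- Share after week 6: 20 to 60%, assumed.
- Missed-indication share: 1 to 10%, assumed.

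Low end: 100 × 0.10 × 0.20 × 0.01 = 0.02. High end: 100 × 0.45 × 0.60 × 0.10 = 2.7.

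A more pessimistic missed share of 10 to 30%, also assumed, at a 25% imaging rate gives 25 × 0.40 × (0.10 to 0.30) = 1.0 to 3.0 with a 40% late share, and 25 × 0.60 × (0.10 to 0.30) = 1.5 to 4.5 with a 60% late share.

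For scale, the protocol's intracluster correlation of 0.088 and cluster size of 25 give a design effect of 1 + 24 × 0.088 = 3.112. The 95% confidence half-width at 25% with 3750 patients is 1.96 × √(0.25 × 0.75 × 3.112 / 3750) = 2.4 points.

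**5. The opposite error**

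About 12% of chiropractors take their own x-rays, which the administrative data do not hold; 0.12 × 50 = 6 of the planned chiropractors. After week 6 these images are known only from patient questionnaires. Images missed in this way lower the rate, in one profession only.

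**The case against.** A reader might infer that indications are recorded for six weeks only, so that all later imaging becomes inappropriate by default. The documents do not support that. Red-flag items recur at 3, 6 and 12 months, linked records capture developing pathology throughout, and the rule uses all sources together. Nor does Table 1 omit most of the Table 3 signs; it matches half. Its list may be only a topic summary: the factor itself names cauda equina syndrome, and the questionnaires in the additional file are not shown, so the full item list cannot be checked.

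A reader might also infer that the primary rate must be inflated overall. That is not shown. The rule sets no expiry on a red flag, so a cancer history recorded at baseline can make a much later image appropriate whatever prompted it. Missed in-house x-rays also lower the rate. The protocol discloses that gap and collects the information from patients as well as on encounter forms.

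The protocol also gives a clinical reason for six weeks, and analysis by period could be left to a statistical analysis plan.

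Part of the concern survives this. The late sources are self-reports up to six months apart and records suited to confirmed disease, whereas the criterion is suspicion. The reason for six weeks supports ending the forms then; it does not show that imaging over the following 46 weeks can be classified equally well. The article itself fixes the windows and the default rule, so the mismatch is not merely a detail deferred to another document.

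**Conclusion.** The concern holds in a limited form. Ascertainment of indications is weaker after week 6, while imaging continues to be counted under the same label. If the plan is followed as written, some later images ordered on justified suspicion, or for a new episode with an unrecorded indication, will be called inappropriate.

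The size cannot be determined from the documents. The illustrative range runs from negligible to about the width of the sampling error (2.7 against a half-width of 2.4 points at a 25% rate), and beyond it only under the more pessimistic assumed shares. The late share and the missed-indication share have no source in the protocol. The net direction is also open, because under-capture of late in-house x-rays works the other way.

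The coverage gap rests on Table 1 reflecting the actual late questionnaire. The administrative gap rests on the more-than-two-visits definition being the one applied. A looser reading of suggestive administrative data would narrow it.

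**What to change.** - Report the inappropriate-imaging rate and the comparison among professions separately for index visit to 6 weeks and for 6 weeks to 12 months.
- Add a sensitivity analysis that either restricts the appropriateness label to imaging up to 6 weeks or treats later images without a completed questionnaire as unclassifiable.
- State how a late image is classified when the corresponding questionnaire is missing.

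All of this uses data already planned. The cost is fewer events in the restricted analysis and slightly more analysis work. Moving the primary outcome itself to six weeks is not required: it would change the quantity estimated, and removing the label from all later imaging would discard two sources that still carry information.
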